### Intervention and control {11a)

The control group will receive standard preoperative care only, while the intervention group will receive standard preoperative care plus VR. Standard preoperative care will include preparing the preoperative surgical site, preoperative bathing, preoperative hair removal, wearing theatre gown, removing all jewellery, correct patient ID bracelet, and completing the patient preoperative checklist and health record.

Standard preoperative care currently does not include routine anxiety screenings and nonpharmacological and pharmacological interventions.

The trial site has more than 17 chairs in the holding area where patients can wait to be called. In that area, there is TV and magazines available upon request.

### Virtual reality intervention {11a}

The participants will be asked to wear the VR headset for 10 min, which has been suggested in the literature to be the optimal time frame for VR without adverse side effects [32, 33]. The participants will be seated in the preoperative holding area while immersed in a VR. The preoperative holding area has been selected for administration of the intervention because evidence suggests preoperative anxiety levels among adult surgical patients peak in the preoperative holding area [34]. The VR will be used for relaxation purposes with nine natural scenes combined with natural sounds and music, for the participant to select from: blue moon, red savanna, blue ocean, green meadows, black beginning, white winter, blue deep, red fall, and the orange sunset (Fig. 2). The participant’s face and forehead will be cleaned using skin-friendly antibacterial cleaning wipes before using the VR device. Disposable hygiene covers will be used to protect the VR device. The researcher will provide the intervention and monitor the participant for adverse side effects such as headache, nausea, vomiting, sweating, fatigue, drowsiness, disorientation, and apathy throughout the session [33].

**Fig. 2 Fig2:**
[figure not shown]
Virtual reality scenes retrieved from https://www.oculus.com/experiences/quest/2616537008386430/

### Criteria for discontinuing the trial in an individual {11b}

The researchers will monitor the participants continuously for side effects. If a side effect occurs, the VR session will be ceased immediately, and a treating medical team will be consulted. Also, there may be a risk of exacerbating the participant’s anxiety level associated with using a survey to assess anxiety. If this is the case, participants to be instructed to stop the survey and appropriate support will be provided by the researcher or medical team.

### Strategies to improve adherence to interventions {11c}

This study includes one-time intervention during the study and is a pragmatic study. The researcher will provide the intervention and the research assistant will collect the data. Researchers will daily check the data in the REDCap™ platform. Also, all researchers share information through periodic meetings (weekly) and discuss the study and appropriate management when problems occur.

### Concomitant care and interventions that are permitted or prohibited during the trial {11d}

There is no care or intervention prohibited during the trial. But we anticipate that some participants may regularly use anti-anxiety/anti-depressant medications. If this is the case, the research assistant will document the name and dose of the medication taken prior surgery.

### *Outcomes {12}*

#### Primary outcome

Perioperative anxiety will be assessed by the Research Assistant at three time points: on admission to the preoperative area (T1), immediately before surgery (T2), and 1 h on arrival to the post-anaesthesia care unit (T3). Participants will be asked to rate their level of anxiety using the visual analogue scale for anxiety (VAS-A). The VAS-A is valid, reliable, and frequently used to evaluate perioperative anxiety levels in surgical populations [35]. The VAS-A consists of a 100-mm horizontal line representing two behavioural extremes at either end of the continuum (i.e., ‘not at all anxious’ = 0, whereas ‘extremely anxious’ = 100). Scores on the VAS-A of 25 or higher reflect significant levels of anxiety [35].

**Figure Figa:**
[figure not shown]
Visual analog scale for anxiety (VAS-A)

### Secondary outcomes

The secondary outcomes to be assessed include:Stress levels will be assessed via two methods:A)Saliva cortisol levels as measured by collecting 4–5 ml of saliva in a clean glass tube. The samples will be labelled with participant ID number and stored at −18°C until they are transferred to Saliva and Liquid Biopsy Translational Laboratory, Queensland University of Technology, for analysis using the Cortisol ELISA Assay Kit™ by an independent laboratory. The analysis results will be intended to determine the quantitative of cortisol by an enzyme immunoassay in human saliva. This is a highly sensitive test, with results changing in minutes after exposure to an anxiety-inducing or relaxing stimulus [26]. The sample will be used for the purposes of this research project only and will be destroyed at the end of this project.Saliva samples will be collected from participants by the Research Assistant at two-time points: on admission to the preoperative area (T1) and immediately before surgery (T2).B)Heart rate (HR) as measured manually for 1 min and the mean HR will be calculated. The Research Assistant will record HR at three time points: on admission to the preoperative area (T1), immediately before surgery (T2), and 1 h on arrival to the post-anaesthesia care unit (T3).Pain level as measured by the visual analogue scale for pain (VAS-P). The Research Assistant will ask the participants to rate their pain on the VAS-P tool at two time points: on admission to the preoperative area (T1) and 1 h on arrival to the post-anaesthesia care unit (T3).Patient satisfaction as measured by the Leiden Perioperative Patient Satisfaction questionnaire (LPPSq). The questionnaire is a valid and reliable tool used to assess and measure different aspects of patient satisfaction with perioperative care with 39 questions [36]. The participants will be asked to complete the questionnaire 24 h after surgery before discharge (T4).Hospital length of stay (LOS) as measured from the date of admission to discharge from hospital. The Research Assistant will collect this data from administrative records post-discharge.Adverse effects of the VR intervention at any time point as measured by the Virtual Reality Symptom Questionnaire (VRSQ). The questionnaire is a valid and reliable measure used to evaluate the possible occurrence of cybersickness symptoms, a type of motion sickness caused by exposure to VR [37]. The researcher will ask the participants in the intervention group to complete the questionnaire immediately before surgery (T2) (Fig. 3, Table 1).

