**Method:**

A two-group parallel randomised controlled trial (RCT) will be conducted, including 150 adult patients (aged 18 years and over) undergoing elective surgery and requiring an overnight stay at a major metropolitan hospital. Eligible participants will be screened for anxiety via the Amsterdam Preoperative Anxiety and Information score (APAIS). Those with moderate to severe anxiety will be randomly allocated to receive the VR session or usual care, in the preoperative holding area. Intervention participants will use a head-mounted VR device to watch and listen to a nature scene for 10 minutes.

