### Inclusion and exclusion criteria {10}

Patients will be eligible for inclusion if they are 18 years old and over, scheduled for elective surgery, can understand English, and can follow instructions. Patients will be excluded if they are scheduled for day surgery, have a history of seizures or motion sickness, have visual impairment, or are unable to complete a self-reported questionnaire.

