
**Fig. 3 Fig3:**
[figure not shown]
Study flow diagram

**Table 1 Tab1:** SPIRIT flow diagram

Study period							
	Pre-admission	Preoperative phase			Postoperative phase		Discharge
Timepoint^a^	−t_1_	t_0_	t_1_	t_2_	t_3_	t_4_	t_5_
Enrolment:							
Eligibility	X						
Informed consent	X						
Screen Anxiety level		X					
Allocation		X					
Interventions:							
VR exposure				X			
Assessments:							
**Primary outcome:**			X	X	X		
Perioperative anxiety							
**Secondary outcomes**:			X	X	X		
Stress level							
Pain			X		X		
Patient satisfaction						X	
Length of hospital stay							X
VR adverse effect				X			

^a^−t_1_, pre-admission; t_0_, on admission to hospital; t_1_, on admission to preoperative area; t_2_, immediately before surgery (holding area); t_3_, 1 h post-surgery; t_4_, after 24 h post-surgery and before discharge; t_5_, post-discharge

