#### Missing data {20c}

Missing data will be handled by complete case analysis. Data collection will occur within the same day and thus missing data should be rare.

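### The only satisfaction time point needs 24 h in hospital after surgery, but eligibility needs only an overnight stay, so earlier discharges have no valid window

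*Protocol article*

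**What the plan says.** **Timing.** The protocol's Secondary outcomes section gives satisfaction a single collection point: "The participants will be asked to complete the questionnaire 24 h after surgery before discharge (T4". The footnote to Table 1 defines the same point as "t_4_, after 24 h post-surgery and before discharge". Neither place offers another route, such as completion at discharge or by telephone, for a patient who has already left.

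**Who is enrolled.** The abstract (Method) describes adults "undergoing elective surgery and requiring an overnight stay". Under Inclusion and exclusion criteria {10}, the only condition on stay is this: "Patients will be excluded if they are scheduled for day surgery". Nothing requires 24 h in hospital after the operation.

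**How the outcome is analysed.** Statistical plan {20a} compares satisfaction by an independent-sample t-test. Missing data {20c} specifies complete-case analysis and gives the reason: "Data collection will occur within the same day and thus missing data should be rare".

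**Length of stay** is a separate secondary outcome: "Hospital length of stay (LOS) as measured from the date of admission to discharge from hospital".

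**The concern.** An overnight stay does not imply 24 h in hospital after surgery. For a patient discharged sooner, the T4 window as written is empty, so the score is missing because of the schedule and not because of refusal or oversight. Complete-case analysis then removes that patient from the satisfaction comparison.

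Two things are at stake. The t-test has fewer patients than were randomised and followed up. The result also describes only patients who stay beyond 24 h, which is a narrower group than the one enrolled. The protocol's reason for expecting few missing values covers T1 to T3 but not T4, so this loss appears not to have been foreseen.

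**Working it through.** **1. Is the window ever empty for an eligible patient?** T4 needs (a) at least 24 h since surgery and (b) the patient still in hospital. Take two patients, both discharged at 10:00 the next day (illustrative times):

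| Surgery | Discharge | Hours after surgery | Overnight stay? | T4 window? |
|---|---|---|---|---|
| 08:00 | 10:00 next day | 26 | yes | yes, 2 h |
| 14:00 | 10:00 next day | 20 | yes | none |

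Both are eligible, but only the first can give a T4 score under the stated rule.

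**2. Does the missing-data premise cover T4?** T1 and T2 precede surgery, and T3 is about 1 h after it, so same-day collection is plausible for them. T4 is at 24 h or later and cannot fall on the day of surgery.

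**3. Loss of precision.** The protocol gives no sample size for satisfaction, so there is no stated figure to reproduce. Its 150 patients (75 per group) are set for the VAS-A with 15% dropout.

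Inputs from the protocol: 75 per group and 15% dropout, so 75 × 0.85 = 63.75, about 64 per arm. Type 1 error is 5% (two-sided assumed).

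Assumed inputs: a share f leaving before 24 h of 20, 30 or 50%, and a true difference of d = 0.5 SD.

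Formulas: n = 64 × (1 − f). Power comes from the two-sample t-test with noncentrality d × √(n/2).

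| f | n per arm | Noncentrality | Power at 0.5 SD | Difference detectable with 80% power |
|---|---|---|---|---|
| 0 | 64 | 2.83 | 80% | 0.50 SD |
| 20% | 51.2 | 2.53 | 71% | 0.56 SD |
| 30% | 44.8 | 2.37 | 65% | 0.60 SD |
| 50% | 32 | 2.00 | 50% | 0.71 SD |

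The base of 64 removes the 15% dropout first. If that allowance already included the early leavers, the base would be 75. The detectable difference (normal approximation, (1.960 + 0.842) × √(2/n)) would then go from 0.46 SD at n = 75 to 0.51, 0.55 and 0.65 SD at n = 60, 52.5 and 37.5.

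**4. Bias between arms.** Suppose satisfaction and postoperative stay are bivariate normal with correlation ρ, there is no true difference in satisfaction, and the shortest-stay share p of an arm is missing. The mean satisfaction of those remaining is ρ × φ(z_p)/(1 − p), in SD units, where z_p is the p-quantile of the standard normal. The factor φ(z_p)/(1 − p) is 0.350 at p = 20%, 0.497 at 30% and 0.644 at 40%. All values of p and ρ below are assumed.

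| Leaving early: control / VR | Bias at ρ = −0.2 | Bias at ρ = −0.4 |
|---|---|---|
| 20% / 20% | 0 | 0 |
| 20% / 30% | −0.2 × 0.147 = −0.03 SD | −0.06 SD |
| 20% / 40% | −0.2 × 0.294 = −0.06 SD | −0.12 SD |

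Under this model, equal shares leaving early give no bias. Bias appears only when the shares differ.

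**The case against.** **The window may be nominal.** The main text can be read as roughly 24 h with discharge as the limit, and nothing says an earlier form would be refused. Staff might well hand it over at discharge, and the full protocol may say so. This softens the point, so the loss is stated only for the schedule followed as written. It does not remove it, because the Table 1 footnote says after 24 h and joins the two conditions. This is a rule the article states, not a detail it leaves out.

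**A reader might infer that VR sends patients home sooner, so that the comparison is no longer randomised.** The protocol does not support this. Its only hypothesis {6b} concerns the VAS-A. The links between anxiety and longer hospitalisation are background, and the Background section reports no significant change in length of stay in the four earlier adult VR studies. Stratification by surgery type also tends to balance short-stay operations across arms.

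**A reader might also infer that the missing patients are simply the fastest recoverers.** The two patients in the working differ only in the hour of surgery. If admitted on the same date, they could have the same recorded length of stay. Part of the loss therefore comes from theatre scheduling, with no evident relation to arm.

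**The size rests on assumptions.** Neither the shares leaving early nor the 0.5 SD target is in the protocol, and no power was promised for satisfaction. This objection stands: the loss could be trivial or large.

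**Conclusion.** The point holds as a defect in a stated collection rule. T4 cannot be met by every patient the trial enrols, no alternative is given, and the premise used to justify complete-case analysis is wrong for T4. If any patients leave before 24 h and the schedule is followed as written, lost precision and a result limited to longer-stay patients follow directly.

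The size is unknown because the protocol does not give the share leaving early. The fall in power from 80% to about 71, 65 or 50% holds only for the assumed shares of 20, 30 and 50% and an assumed 0.5 SD effect. Bias between arms is conditional on VR changing early discharge and is not established. Even the assumed splits of 20% against 30% or 40% give only about 0.03 to 0.12 SD.

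This concerns one secondary outcome, and the primary outcome is unaffected. It should be corrected because the correction is easy, but it does not threaten the trial's main conclusion.

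**What to change.** 1. In Secondary outcomes and in the Table 1 footnote, define T4 as 24 h after surgery or at discharge, whichever comes first.
2. Record the date and time each questionnaire is completed, so that the spread of timing can be reported by arm.
3. In Missing data {20c}, limit the same-day statement to T1 to T3, and say that T4 is collected later and what loss is expected there.

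The cost is a change of wording, one extra recorded field and a prompt at discharge. The downside is that questionnaire timing then varies with discharge time, itself determined after randomisation, and some forms will be completed earlier than 24 h. That is preferable to having no score for those patients, and the recorded times make the variation visible.

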
**Fig. 3 Fig3:**
[figure not shown]
Study flow diagram

**Table 1 Tab1:** SPIRIT flow diagram

Study period							
	Pre-admission	Preoperative phase			Postoperative phase		Discharge
Timepoint^a^	−t_1_	t_0_	t_1_	t_2_	t_3_	t_4_	t_5_
Enrolment:							
Eligibility	X						
Informed consent	X						
Screen Anxiety level		X					
Allocation		X					
Interventions:							
VR exposure				X			
Assessments:							
**Primary outcome:**			X	X	X		
Perioperative anxiety							
**Secondary outcomes**:			X	X	X		
Stress level							
Pain			X		X		
Patient satisfaction						X	
Length of hospital stay							X
VR adverse effect				X			

^a^−t_1_, pre-admission; t_0_, on admission to hospital; t_1_, on admission to preoperative area; t_2_, immediately before surgery (holding area); t_3_, 1 h post-surgery; t_4_, after 24 h post-surgery and before discharge; t_5_, post-discharge

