### Screening

Patients who meet the above inclusion criteria will be screened for their anxiety level using a validated tool—the Amsterdam Preoperative Anxiety and Information score (APAIS) [28, 29]—on the day of their surgery in the preoperative holding area. Patients with moderate to high preoperative anxiety levels—described by preoperative anxiety score ≥11 [30]—will be included in the study and randomised to the intervention or control group.

The APAIS is a rapid and clinically practical assessment tool developed by Nelly Moerman and previously validated against other scales to evaluate patients’ preoperative anxiety with good sensitivity and strong specificity for clinically significant anxiety [28, 29]. It consists of six questions in total. Each question is rated on a 5-point Likert scale from “not at all” to “extremely”. The sum of scores from questions 1, 2, 4, and 5 show the anxiety level, while the sum of scores from questions 3 and 6 show the level of information required by each individual. A patient with a score of 11 or more (scoring range from 4 to 20) on the anxiety scale experiences anxiety and requires further intervention [28, 29, 31]. On the need for information scale, patients scoring 2–4 are categorised as having minimal or no need for information, patients scoring 5–7 are categorised as having an average need for information, and patients scoring 8–10 are considered as having high need for information [28, 31].

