### Blinding {17b}

The Research Assistant involved in outcome data collection will be blinded to group allocation, as will the statistician who will conduct the data analysis. Clinicians (nurses, doctors, and other health providers) will not be told who is participating in the study nor their group allocation; however, it is acknowledged that it is not possible to prevent participants from sharing this information with them.

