### Statistical plan {20a}

Characteristics of groups will be summarised using counts and percentages for categorical variables and means and standard deviations for continuous variables. The primary outcome (anxiety at Time 2 and Time 3 in stacked format) will be compared between groups at each follow-up time point using a linear mixed-effects regression model, with fixed effects including treatment arm time (categorical), the interaction between treatment and time, anxiety time point (either Time 2 or Time 3), surgical type (stratification variable), and the baseline value of the outcome variable. Differences in mean VAS-A scores between groups at each time point will be presented together with 95% confidence intervals and *p*-values. Continuous secondary outcomes with repeated measurements will be compared using the same model. Hospital length of stay will be compared using the rank-sum test. Patient satisfaction will be compared using an independent sample *t*-test and descriptive statistics will be used to summarise the VRSQ.

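### Table 1 schedules allocation before the baseline measurements, the Screening section implies a different timetable, and nothing secures the T1 baseline before randomisation

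*Protocol article*

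**What the plan says.** Table 1 (SPIRIT flow diagram) has the rows "Screen Anxiety level" and Allocation ticked under t0. Perioperative anxiety, stress level and pain have their first tick under t1, and VR exposure is ticked under t2. The footnote orders the first two time points: "t_0_, on admission to hospital; t_1_, on admission to preoperative area".

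The Screening section says that the APAIS is administered "on the day of their surgery in the preoperative holding area", and that patients scoring 11 or more "will be included in the study and randomised to the intervention or control group". It does not mention T1. The Primary outcome and Secondary outcomes sections place T1 on arrival in the preoperative area, without relating it to allocation. The section on randomisation and allocation concealment hides the allocation from the researcher until eligibility and screening are settled; it does not require T1 to be complete.

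The Statistical plan includes among the fixed effects of the primary model surgical type "and the baseline value of the outcome variable", and applies the same model to continuous secondary outcomes with repeated measurements.

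The Blinding section covers the Research Assistant who collects outcomes and the statistician. Participants are not listed. Of clinicians, it concedes that "it is not possible to prevent participants from sharing this information with them".

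**The concern.** Baseline adjustment is safe when the baseline cannot have been affected by the randomised assignment. Measuring before allocation guarantees this. A self-rated anxiety score taken after a person learns whether they will get the headset does not carry that guarantee: it could move with relief or apprehension in one arm, or disappointment in the other. Adjusting for a covariate that has moved this way removes part of a real difference or adds a spurious one, and a larger sample does not cure it.

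The protocol treats these measures as reactive. Its discontinuation section allows that an anxiety survey may itself raise anxiety, and its cortisol description says that levels respond within minutes to a stressful or calming stimulus. The only explicit schedule shown puts allocation first, so the question bears directly on a covariate of the primary model.

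**Working it through.** **Order of events.** The protocol states no figure on this point, so the first step is to set the sections side by side.

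| Source | Screening and allocation | T1 baseline | Order implied |
|---|---|---|---|
| Table 1 and footnote | t0, hospital admission | t1, preoperative area | Allocation first |
| Screening, with Primary outcome | Holding area, day of surgery | On arrival in the preoperative area | Not stated |
| Randomisation and concealment | After eligibility and screening | Not mentioned | Not stated |

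Screening cannot take place both on admission to hospital and in the holding area unless these are the same moment, and the footnote separates t0 from t1. If the preoperative area and the holding area are the same place, T1 on arrival could come before or after allocation. If they are different places, as the footnote may suggest by attaching the holding area to t2, T1 could come first. No section shown states that T1 precedes allocation.

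**Size of the bias, if there is one.** Let the true effect be τ (VR minus control, negative is benefit), the within-arm slope of outcome on baseline be β, and the T1 difference caused by knowing the allocation be δ (VR minus control). Then

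adjusted effect ≈ τ − β × δ, so bias ≈ −β × δ.

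The 20-point target comes from the Hypothesis section. β and δ are not in the document and are assumed:

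- Low end: 0.5 × 3 = 1.5 points, and 1.5 / 20 = 7.5% of the target.
- High end: 0.7 × 5 = 3.5 points, and 3.5 / 20 = 17.5% of the target.
- δ = 0: no bias, even if T1 is taken after allocation.

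A simulated analysis of covariance checked the formula. It used 64 per arm (75 × 0.85 = 63.75, rounded up), true effect −20 and an assumed SD of 25. Mean adjusted effects were:

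| δ | β = 0.3 | β = 0.5 | β = 0.7 |
|---|---|---|---|
| −10 | −17.0 | −15.1 | −12.9 |
| −5 | −18.5 | −17.5 | −16.5 |
| 0 | −19.9 | −20.0 | −19.9 |
| +5 | −21.6 | −22.4 | −23.3 |

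These agree with −20 − βδ to within simulation error. For example, β = 0.5 and δ = −5 give −20 + 2.5 = −17.5. The SD does not enter the formula, so the assumed 25 does not drive the result. Adjusting for the unshifted baseline returned about −20 in every case.

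**The case against.** The tempting stronger reading is that the primary model does adjust for a post-randomisation value reported by participants who know their arm. A reader might infer this from Table 1, but the document does not establish it, for these reasons:

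- The t0 label disagrees with the Screening text, so the table cannot by itself settle what happens at the site. The study flow diagram (Fig. 3), which might settle it, is not shown. Table 1 may be a drafting slip.
- No section says when participants learn their group. The remark in the Blinding section concerns participants telling clinicians and gives no time. Allocation in REDCap is not the same as disclosure to the participant.
- Only VAS-A and VAS-P are self-reported. Cortisol is assayed by an independent laboratory and heart rate is counted by the blinded Research Assistant, although knowing the allocation could still affect either.
- VR follows T1 in the table, so T1 is pre-treatment on any reading.
- The size rests on assumed inputs. Relief in the VR arm or disappointment among controls would make δ negative and attenuate the effect, which is conservative in a superiority trial. Apprehension in the VR arm would inflate it.

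All of this stands and limits the point to a conflict with a conditional risk of bias. It does not remove the conflict, and it does not supply the missing safeguard. Characteristics fixed before randomisation (APAIS, age, sex, surgery type) are not at risk; only the T1 measurements are.

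**Conclusion.** The point holds in a limited form. Table 1 and the Screening section give incompatible timetables, and no section secures T1 before allocation. Under Table 1 as written, the baseline covariate of the primary model, and of the repeated continuous secondary outcomes, is measured after randomisation in a trial that does not blind participants.

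Bias requires two further conditions that the document neither confirms nor rules out: participants know their arm by T1, and this shifts the measurement. If both hold, the illustrative size is 1.5 to 3.5 points of the 20-point target, with direction unknown in advance. If either fails, the bias is zero and only the document needs correcting. Severity: should fix, before the primary analysis.

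**What to change.** Reconcile Table 1 with the sections on screening, randomisation and the primary outcome so that all give one order: APAIS screen; all T1 measurements (VAS-A, saliva, heart rate, VAS-P); then REDCap randomisation and disclosure to the participant. Lock the randomisation step until the T1 form is saved.

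Recruitment began on 10 November 2021, so for participants already enrolled compare the T1 and allocation timestamps. If T1 came first, correcting the text is enough. If allocation came first, add a sensitivity analysis that adjusts for the APAIS anxiety score in place of T1 VAS-A. APAIS determines eligibility and therefore precedes randomisation. It is a weaker covariate: it is a different instrument, and eligibility restricts it to 11–20 of its 4–20 range.

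The sample size stays at 150, and no extra measurement or staff is needed. The cost is re-ordering the REDCap forms and a small amendment that, under the protocol's own rule, goes to the ethics committee while recruitment is under way.
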